### Strategies to improve adherence to interventions {11c}

All participants for this trial will receive a total of four psychological based interventions (see the ‘Intervention description {11a}’ section). Each intervention session lasts for 60 min. To ensure patient adherence to the study interventions during the trial period, all participants will be well-informed during the consent process. The study participation burden, such as duration and timing of each psychology session, and completion of primary outcome questionnaires at 1 and 3 months post-surgery will be explained. The senior pain psychologist responsible for screening potential study participants will record all eligible candidates and those that do not proceed with the study due to ineligibility, non-consent, or withdrawal. In so far as it is possible, only eligible and fully willing individuals will proceed to randomisation and allocation of the patient to either the CBT-CP or PEM group.

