### Sample size {14}

The primary outcome is the difference in the BPI average pain severity score between the study groups, three months after surgery. A clinically important difference on the BPI is 2 raw score reduction on the 11-point Numerical Pain Rating Scale (NRS) [22–24]. The standard deviation (SD) of BPI scores after breast surgery is in the order of 2.3 [25] on this scale. Taking a BPI score reduction of 2 as the minimal clinically relevant difference, then *n* = 21 patients would be required each arm if type I error = 0.05 and type II error is 0.2 (power 80%). This calculation was verified by using an online power calculator (https://www.sealedenvelope.com/power/continuous-superiority/). The screening process for potential eligible participants will be a very thorough methodological process. As mentioned in the exclusion criteria, any suspected non-compliant participants will not be enrolled or randomised to either of the study’s intervention. By taking this approach, we endeavour to limit the number of dropouts to approximately 10%, and therefore, we propose to enrol 24 eligible patients in each group (*N* = 48 total).

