### Statistical methods

#### Statistical methods for primary and secondary outcomes {20a}

Outcome analyses will be conducted by researchers (MBC and DB) who will be blinded to treatment group allocation. Descriptive statistics will be calculated for all outcome measures at each time point, including for continuous variables: means, standard deviations or medians with ranges of scores, and for categorical variables: frequencies and percentages.

Descriptive and inferential statistics will be obtained using the appropriate statistical methods required to address the study objectives. The primary analysis will compare the effect of the interventions on the primary outcomes; average pain severity at 3 months post-surgery. Outcome analyses will be conducted according to an intention to treat principle, i.e. all randomised participants will be included in the main analysis and will be analysed as randomised, regardless of protocol adherence. Secondary analysis will involve the analysis of the secondary outcomes: QoR-15 at 24 h post-surgery, PCS, HADS and average pain interference on the BPI short form at 3 months post-surgery. Linear mixed models on the outcome measures over time will be fitted to evaluate the effectiveness of both interventions, which intrinsically adjusts for baseline scores. Statistical significance will be assessed from a *p*-value < 0.05 from the group by time interaction term. For all tests, 2-sided *p*-values will be used, which will be reported to 4 decimal places with *p*-values less than 0.001 reported as *p*< 0.001. In the case of a significant result, contrasts of the group effects at each assessment time point will be used to investigate the direction and pattern of effects. Irrespective of statistical significance, the mean changes and confidence intervals will be reported. An up-to-date version of SPSS will be used to conduct analyses.

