#### Methods for additional analyses (e.g. subgroup analyses) {20b}

A per-protocol analysis will exclude participants found to be ineligible after randomisation and those who did not receive the intervention. Both intention to treat and per-protocol analyses will be reported and superiority will be determined only if demonstrated with the primary intention to treat analysis.

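### Superiority is decided by a group-by-time interaction over baseline, 1 and 3 months, not by the 3-month difference the trial is designed and sized for

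*Protocol article*

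**What the plan says.** - **Target.** Section {14}: "The primary outcome is the difference in the BPI average pain severity score between the study groups, three months after surgery". Section {20a} repeats it: "The primary analysis will compare the effect of the interventions on the primary outcomes; average pain severity at 3 months post-surgery". The Objectives {7} and Outcomes {12} sections name the same 3-month time point.
- **Model.** Section {20a}: "Linear mixed models on the outcome measures over time will be fitted to evaluate the effectiveness of both interventions, which intrinsically adjusts for baseline scores". Baseline is therefore one of the modelled times.
- **Decision rule.** Significance is read from a p-value below "0.05 from the group by time interaction term".
- **Role of the visit contrasts.** "In the case of a significant result, contrasts of the group effects at each assessment time point will be used", to describe the direction and pattern of effects. Mean changes with confidence intervals are reported whether or not the result is significant.
- **Visits.** Table 2 marks BPI at allocation, 30 days and 90 days. Section {11c} agrees: "completion of primary outcome questionnaires at 1 and 3 months post-surgery".
- **Superiority.** Section {20b}: "superiority will be determined only if demonstrated with the primary intention to treat analysis".

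**The concern.** The objective, the primary outcome and the sample size all concern one contrast: the arms' difference in pain severity at 3 months. The only stated significance criterion tests something else, namely whether the difference between arms changes at all across three visits.

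Two wrong conclusions become possible. A benefit at 1 month that has gone by 3 months can meet the criterion, although the trial is about chronic pain at 3 months. A genuine 3-month benefit can fail it, because a second degree of freedom is spent on the 1-month pattern, and the formal 3-month contrast is then not tested. In either case the p-value that settles superiority does not answer the primary objective.

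**Working it through.** **1. Reproduce the plan's sample size.** Inputs from section {14}: difference 2, SD 2.3, alpha 0.05 (two-sided, from {20a}), power 80%, dropout 10%.

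n per arm = 2 × (1.960 + 0.842)² × 2.3² / 2² = 20.76, rounded up to 21. With dropout, 21 / 0.9 = 23.3, rounded up to 24. Both figures match the plan. Power at 21 per arm is 80.4% by the normal formula and 78.5% by the t distribution. This is the power of a two-group comparison at one time point.

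**2. Power of the interaction.** Assumptions not in the document: SD 2.3 at every visit, 21 completers per arm, no true baseline difference, time as categories, and equal correlation ρ between any two visits (compound symmetry). With true differences d1 at 1 month and d3 at 3 months, the 2-df test on the changes from baseline has non-centrality

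λ = n (d1² − d1·d3 + d3²) / (3 σ² (1 − ρ)), with n = 21 and σ² = 5.29,

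referred to a non-central F with 2 and 39 df (5% critical value 3.24).

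- Effect at 1 month only (d1 = 2, d3 = 0): λ = 21 × 4 / (15.87 × (1 − ρ)) = 5.29 / (1 − ρ).
- Growing effect (d1 = 1, d3 = 2): λ = 21 × 3 / (15.87 × (1 − ρ)) = 3.97 / (1 − ρ).

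**3. Comparator.** The 3-month contrast adjusted for baseline has residual SD 2.3 × √(1 − ρ²). For a 2-point difference its non-centrality is 2 / (2.3 × √(1 − ρ²) × √(2/21)), that is 2.82, 2.95, 3.25 and 3.95 for ρ = 0, 0.3, 0.5 and 0.7 (t distribution, 39 df).

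**4. Results: probability of p < 0.05.**

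| ρ | Interaction, effect at 1 month only (2, then 0) | 3-month contrast, same truth | Interaction, growing effect (1, then 2) | 3-month contrast, same truth |
|---|---|---|---|---|
| 0 | 49.5% | 5% | 38.5% | 78.5% |
| 0.3 | 65.5% | 5% | 52.5% | 82.1% |
| 0.5 | 80.7% | 5% | 67.8% | 88.7% |
| 0.7 | 96.0% | 5% | 89.0% | 97.0% |

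**5. Checks.**
- Simulation (20,000 trials per scenario) agrees. With the growing effect, the 3-month contrast was significant and the interaction was not in 31%, 22% and 8% of trials at ρ = 0.3, 0.5 and 0.7.
- If correlation decays with time (AR(1), ρ = 0.3, 0.5, 0.7), the growing effect gives the interaction 42%, 50% and 67%, against 79%, 81% and 88% for the 3-month contrast. The 1-month-only effect triggers the interaction in 70%, 88% and 99%.
- The growing effect (1, then 2) is the least favourable pattern for the interaction under compound symmetry when d3 = 2. With d1 = 0 or 2, interaction power is 65.5%, 80.7% and 96.0% at ρ = 0.3, 0.5 and 0.7.

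**6. Other ways to code time.** With linear time, the interaction is a difference in slopes. With baseline as a covariate, it compares only 1 month with 3 months and has 5% power for a constant 2-point benefit. It equals the 3-month effect (as a difference in change) only if baseline and 3 months are the sole times in the model, which Table 2 does not support.

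**The case against.** The strongest reply is that section {20a} should be read as a whole. It defines the primary analysis as a comparison at 3 months, section {20b} ties superiority to that analysis, and visit contrasts follow a significant interaction. If a claim needed both a significant interaction and a significant 3-month contrast, a 1-month-only effect could produce a false claim in at most 5% of trials. Mean changes and intervals are also reported regardless, so the 3-month result would not be hidden. The coding of time is not stated and might be left to an analysis plan. Finally, the figures depend on the scenario: a transient effect of 1 point rather than 2 triggers the interaction in only 20%, 27% or 42% of trials at ρ = 0.3, 0.5 or 0.7, and at ρ = 0.7 the interaction has 89% power even in its least favourable pattern.

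Part of this stands. Only the formal contrasts are gated, not the estimates. A missed effect is a risk that depends on the correlation and on the 1-month effect. Type I error with no effect at any visit remains 5%.

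The core does not stand. The two-step rule is written nowhere: the contrasts are there to describe direction and pattern, and no sentence makes superiority depend on the 3-month one. Even if it were written, it would leave the loss of power untouched. Nor is this detail left to an analysis plan, since the protocol states a criterion and that criterion conflicts with its own primary outcome.

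**Conclusion.** The concern holds, and the rule should be corrected before unblinding. The sample size is right for the 3-month comparison, but the criterion that decides the trial is a different test. Over correlations of 0 to 0.7 under compound symmetry, with SD 2.3 and 21 completers per arm, a 2-point effect confined to 1 month meets the criterion in about 50% to 96% of trials. A true 2-point effect at 3 months, preceded by 1 point at 1 month, is detected with about 39% to 89% power, against 79% to 97% for the baseline-adjusted 3-month contrast. These figures rest on an assumed correlation and on chosen effect patterns. The mismatch between test and objective does not: it follows from the text and the visit schedule.

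**What to change.** In section {20a}, state that the single primary test is the between-group difference in BPI average pain severity at 3 months, estimated as the 3-month contrast from the repeated-measures mixed model, two-sided at 0.05 with a 95% confidence interval. Remove the interaction p-value as the significance criterion and as the gate to the contrasts. Report the interaction and the 1-month contrast as supportive. In {20b}, tie superiority explicitly to the 3-month contrast.

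Say also how baseline enters the model: as a covariate, or as an outcome with a common mean in both arms. A plain difference in change from baseline would have only 64%, 79% and 94% power at ρ = 0.3, 0.5 and 0.7 (compound symmetry), against 82%, 89% and 97% with adjustment.

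The cost is one paragraph in the protocol or analysis plan, dated before unblinding. No new data are needed, and 21 per arm (24 enrolled) remains adequate.

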#### Interim analyses {21b}

No interim analyses will be conducted.

#### Methods for additional analyses (e.g. subgroup analyses) {20b}

A per-protocol analysis will exclude participants found to be ineligible after randomisation and those who did not receive the intervention. Both intention to treat and per-protocol analyses will be reported and superiority will be determined only if demonstrated with the primary intention to treat analysis.

#### Methods in analysis to handle protocol non-adherence and any statistical methods to handle missing data {20c}

Careful attention will be paid to ensure that all participants are fully assessed at all time points to minimise missing data. We do not plan to use additional statistical methods such as multiple imputation as studies have demonstrated that linear mixed modelling is sufficient to control for missing data [29, 30]

#### Plans to give access to the full protocol, participant level-data and statistical code {31c}

The collated data collected by the investigators will be retained for a maximum 5 years after analysis has been completed. We will deliver a completely de-identified data set an appropriate data upon reasonable request and in agreement with the principal investigator and data protection officer.

### Oversight and monitoring

#### Composition of the coordinating centre and trial steering committee {5d}

This is a single-centre study. The trial steering committee will consist of the principal investigator (DB), trial coordinator (HK) and personnel responsible for data entry and data management (AM, CE and MBC). In addition, a research nurse employed by the institution will also be a member of this committee (HK). This committee will meet monthly to evaluate the progress of the trial, address ongoing organisational and logistical issues and consider any adverse effects.

#### Composition of the data monitoring committee, its role and reporting structure {21a}

During the process of obtaining ethical approval for this single site study, a data protection impact assessment (DPIA) screening tool was completed. This was analysed by the hospital’s data protection officer (DPO) in MMUH. It was deemed that this study posed a low risk to the rights and freedoms of natural persons and therefore a formal DPIA was not needed. Recruitment of participants is expected to be completed within less than 9 months or once the required number of participants needed is fulfilled. Due to the rapid expected inclusion of participants and the known minimal inherited risks associated with this trial, a data monitoring committee was not appointed.

#### Adverse event reporting and harms {22}

The study interventions associated with this trial does not involve any physical interventions, and all patients will receive standard of care during their perioperative period. Therefore, it is not expected that any participants that volunteer to take part in this trial will suffer from any physical complications directly related from this study. However, some participants may find the study interventions (cognitive behavioural therapy or education and mindfulness) distressing. This is not expected, but in the event if this occurs, it will be reported to the principal investigator. The participant will be removed from the trial if merited and further support will be provided.

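### Removal of distressed participants from the trial is not reconciled with stopping the intervention or with intention-to-treat, and {20c} calls the mixed model sufficient without its missing-at-random condition

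*Protocol article*

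**What the plan says.** Four sections of the protocol article bear on what happens to a participant who becomes distressed.

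- **Adverse event reporting and harms {22}** accepts that "some participants may find the study interventions (cognitive behavioural therapy or education and mindfulness) distressing". It continues: "This is not expected, but in the event if this occurs, it will be reported to the principal investigator". The consequence is then "The participant will be removed from the trial if merited and further support will be provided".
- **Criteria for discontinuing or modifying allocated interventions {11b}** lists worsening mental health or psychological well-being, but as a ground for discontinuing the intervention. It does not mention leaving the trial.
- **Statistical methods {20a}** defines intention-to-treat: "all randomised participants will be included in the main analysis and will be analysed as randomised, regardless of protocol adherence". The model is also fixed there: "Linear mixed models on the outcome measures over time will be fitted to evaluate the effectiveness of both interventions".
- **Non-adherence and missing data {20c}** opens with an aim of full assessment of all participants at every time point. It then says "We do not plan to use additional statistical methods such as multiple imputation", on the ground that "studies have demonstrated that linear mixed modelling is sufficient to control for missing data".

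No section says whether questionnaires are still sought after a participant is discontinued or removed.

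**The concern.** Stopping sessions and leaving the trial are different events for the analysis. A participant who stops sessions but still completes the questionnaires fits the intention-to-treat promise. One who leaves the trial ordinarily has no further outcomes, and the promise can then be kept only in form. The protocol uses both descriptions for what looks like the same situation and does not say which applies to data collection.

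The trigger is distress with the allocated treatment. Anxiety, depression and catastrophising are secondary outcomes, and the Background treats psychological state as a driver of post-surgical pain. Outcomes lost for this reason could well be worse than the model would predict. A likelihood-based linear mixed model gives valid estimates when data are missing at random given what was observed. It does not deal with missing data in general, and the protocol does not state the condition. If one arm lost more such participants, that arm would look better than it is on pain and mood.

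**Working it through.** **Step 1: what a removed participant contributes.** Table 1 puts the last session at 1–2 weeks after surgery. Table 2 puts BPI at allocation, 30 and 90 days; PCS at enrolment, 30 and 90 days; HADS at 30 and 90 days only; and QoR-15 at 24–48 h after surgery. If removal during the sessions ends follow-up:

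| Outcome | Data available |
|---|---|
| BPI | baseline only |
| PCS | baseline only |
| HADS | none |
| QoR-15 | none if removed before surgery |

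For BPI and PCS the mixed model can keep her through the baseline value. Missing at random then requires that, given arm and baseline, her unseen pain is no different from that of women who stayed. There is no on-study pain score to support this. For HADS she cannot enter the model at all.

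**Step 2: the plan's own figures.** From Sample size {14}: difference 2, SD 2.3, alpha 0.05, power 80%; tests are two-sided per {20a}.

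n per arm = 2 × 2.3² × (1.960 + 0.842)² / 2² = 20.76, so 21. Dropout: 21 / 0.9 = 23.3, so 24 per arm and 48 in total. Both figures reproduce. The allowed 10% of 24 is 2.4, or about 2–3 per arm from all causes.

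**Step 3: illustrative size.** The protocol gives no removal rate and no outcome gap, so both are assumptions. Let k of 24 in one arm be removed and none in the other. Let d be the amount by which their unseen 3-month BPI exceeds what the model predicts.

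True arm mean = [(24 − k) × m + k × (m + d)] / 24 = m + k × d / 24, where m is the model's mean. The arm is understated by k × d / 24. The approximate two-sided type I error uses SE = 2.3 × √(1/(24 − k) + 1/24), which is 0.67, 0.68 and 0.69 for k = 1, 2 and 3.

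| k | d = 2: shift (share of 2-point target; type I error) | d = 4: shift (share; type I error) |
|---|---|---|
| 1 | 1 × 2/24 = 0.08 (4%; 0.05) | 1 × 4/24 = 0.17 (8%; 0.06) |
| 2 | 2 × 2/24 = 0.17 (8%; 0.06) | 2 × 4/24 = 0.33 (17%; 0.08) |
| 3 | 3 × 2/24 = 0.25 (12.5%; 0.07) | 3 × 4/24 = 0.50 (25%; 0.11) |

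With d = 1 the shift is only 1/24 = 0.04 to 3/24 = 0.13. With equal k and d in both arms the two shifts cancel.

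**The case against.** The case on the other side has weight.

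- **Follow-up may continue.** Section {22} does not say that questionnaires stop or that collected data are discarded, and {20c} aims at full assessment of everyone. Read with {20a}, the default could be complete follow-up. This stands, and the loss of data is therefore a conditional consequence. It does not settle which reading applies.
- **Such removals may be rare.** Distress is described as not expected, and removal applies only if merited. This stands, and it limits the likely size.
- **Nothing points to one arm.** Section {22} names both interventions as possibly distressing, and both arms have four 60-minute sessions with the same psychologist. The one-arm calculation is a worst case. The 10% dropout allowance covers all causes, and a gap of 2–4 points is large against an SD of 2.3. This stands too.
- **Sensitivity analyses are often left to the SAP.** That would answer a complaint about silence. Here, however, {20c} takes a position: it calls the model sufficient and plans no additional methods on that ground.

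A reader might infer that the unblinded psychologist triggers removals, so that missingness must depend on arm. The protocol does not say who reports distress, only that it goes to the principal investigator. A reader might also infer that harm would go unseen because there is no data monitoring committee. The steering committee meets monthly and considers adverse effects, so the text does not support that either.

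**Conclusion.** The point holds as a conflict of wording with a conditional statistical consequence. Sections {11b}, {22}, {20a} and {20c} do not agree on whether a distressed participant stops sessions or leaves the trial, and they need reconciling. If removal ends follow-up, it creates missing outcomes plausibly related to the outcome itself, and the sufficiency claim in {20c} is wrong as worded because it omits the missing-at-random condition.

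The size is unknown and probably small. The range of 0.08–0.50 BPI points rests on three assumptions: 1–3 removals, all in one arm, and a gap of 2–4 points beyond the model's prediction. The largest shift shown is under one standard error (0.50 against 0.69). It would be wrong to conclude that intention-to-treat is certainly broken or that one arm is certainly favoured; the documents establish neither. The sample size is not affected.

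**What to change.** 1. In {11b} and {22}, leave the clinical decision to stop sessions as it is. Add that a participant who stops sessions remains in follow-up for the 30- and 90-day questionnaires unless she withdraws consent to data collection. This brings both sections into line with {20a} and with the full-assessment aim in {20c}.
2. In {20c}, replace the sufficiency claim with a statement that the linear mixed model is valid under missing at random. Add one delta-adjusted sensitivity analysis of 3-month BPI, with missing values shifted by arm (for example 0 to +2 points) and the shift that would reverse the conclusion reported.

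Reporting removals by arm with reasons is good practice but is not part of the point itself.

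The cost is a few sentences, one extra analysis, and a few questionnaires sought from participants who have stopped sessions. Enrolment stays at 24 per arm.
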